Internationally, the prevalence of GDM varies from 1 to 28% depending on the ethnic composition and prevalence of T2DM of the background population, local GDM screening strategies and diagnostic criteria [15–17]. This variation in screening and diagnostic approaches has made global comparisons of GDM prevalence and outcomes problematic. In order to progress towards a universal standard approach to GDM diagnosis, the World Health Organisation (WHO) recommended in 2013 that a 2-h 75 g oral glucose tolerance test (OGTT) should be used, with three time points blood testing (fasting, 1- and 2-h) [1]. These 2013 WHO criteria define GDM as ≥5.1, ≥10.0 and/or ≥ 8.5 mmol/L fasting, 1-h and/or 2-h thresholds. These cut-off values are based on a ≥ 75% adjusted excess risk of adverse neonatal outcomes (e.g. large for gestational age (LGA), foetal hyperinsulinemia), based on data from the Hyperglycaemia and Adverse Pregnancy Outcomes (HAPO) study involving 25,505 women from nine countries [18]. There has been debate over the merits of these new criteria as the number of women diagnosed with GDM would be expected to increase by 15–30%, raising concerns over their cost and clinical effectiveness [19–22]. While the thresholds are based upon calculated excess risk, the decision to base the diagnostic criteria on ≥75% excess risk was based upon consensus. Some countries (e.g. Canada, Norway) have reduced GDM numbers by using thresholds based upon a ≥ 100% excess risk of adverse neonatal outcomes (5.3- and/or 10.6- and/or 9.0 mmol/L, respectively) [23, 24]. Others have not based their criteria on HAPO data at all (e.g. England, New Zealand).

Older Swedish GDM criteria are based on varying cut-off values. If a fasting threshold was used (not used in one region), then ≥7.0 mmol/L was considered GDM. The 2 h criteria ranged from 9.0–11.1 mmol/L, using either capillary or venous samples. Using these criteria, 1–3% of the 115, 000 births were complicated by GDM annually. In June 2015, following a review of the available evidence, the Swedish National Board of Health and Welfare (SNBHW) recommended a move to the 2013 WHO diagnostic criteria, using venous sampling. The SNBHW made no recommendations in relation to the screening (e.g. universal vs risk factor).

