## Methods

### Study design

The Changing Diagnostic Criteria for Gestational diabetes (CDC4G) in Sweden study is a national prospective, unblinded, SW-CRCT of the switch from the former Swedish diagnostic criteria to the WHO 2013 criteria for GDM i.e. to the 3 point OGTT with fasting plasma glucose, 1-h and/or 2-h diagnostic thresholds of ≥5.1, ≥10.0, ≥8.5 mmol/L, respectively (Fig. 1). Each participating centre constitutes one cluster, in which the patients continue to undergo screening for GDM following their usual approach, see Table 1. The time of transition to the new criteria is randomised and subsequently rolled out until all 11 clusters (i.e. centres) implement the new GDM regimes during 2018, see Fig. 2. The transition necessitated the introduction of a fasting glucose sample in one region, and a 1-h sample across all 11 regions. This means that a total population evaluation of the change is required, as many women with GDM diagnosed by the new criteria, will not be identified during the control period (e.g. those without the 1-h test). A sub-analysis among those with untreated and treated GDM by the WHO 2013 is also planned.

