**Fig. 1 Fig1:**
[figure not shown]
Time of preparation, set up, control and intervention in the CDC4G study during 2017, 2018 and 2019. Q = quartile, 3 months period

**Table 1 Tab1:** List of included regions and methods for diagnosing GDM

Centres	Number of births 2017^a^	Indication for a diagnostic OGTT									Diagnostic criteria prior to switch (mmol/L)	Method for glucose analysis
		Previous				BMI at booking	FH^d^	Polyhyd ramnios	Accelerated fetal growth	RPG		
		GDM	Macro somia^b^	LGA^c^	Stillbirth							
1. Stockholm	28,602	T1 & 24–28	24–28			≥35		Yes	Yes	RPG^e^ ≥ 9 mmol/L at booking, week 25, 29, 32/33, 37/38.	FPG < 7.0 and 2-h PG 8.9–11.1	Roche Cobas Beckman Coulter Au. Siemens Advia (hexokinase)
2. Örebro	3565	24–28	24–28			≥35	24–28	Yes	Yes-within 3 days	RPG^e^ ≥ 9 mmol/L at booking, week 24, 28/29, 33, 37.	FPG < 7.0 and 2-h PG 8.9–11.0	Siemens Advia (hexokinase)
3. Västmanland	3120	24–28	24–28			> 35		Yes	Yes	RPG^e^ ≥ 9.0 mmol/L at booking week 25, 30, 35.	FPG < 7.0 and 2-h PG 8.9–11.	Beckman Coulter Au (hexokinase)
4. Dalarna	3232	12–14/24–28	24–28	24–28		> 35	24–28	Yes	Yes	RPG^e^ ≥ 9.0 mmol/L at booking, week 24, 28/29, 33, 37.	FPG < 7.0 and/or 2-h PG 8.9–11.1	Siemens Advia (hexokinase)
5. Uppsala	4200	12–14/24–28	24–28	24–28		≥35	24–28	Yes	Yes	RPG^e^ ≥ 8.8 mmol/L at booking, week 25, 28/29, 33, 37	FPG ≥7.0 and/or 2-h PG ≥10.0	Abbott Architect (hexokinase)
6. Göteborg	9550	25–29	25–29	25–29		≥35	25–29	Yes	(Yes)	Within 1 week if RPG^e^ 8.0–12.1 mmol/L at first antenatal care visit, week 25, 28–29, 35–36.	FPG ≥7.0 and/or 2-h PG ≥10.0 RPG^c^ ≥ 12.2	Nova Biomedical StatStrip TM Multi-Well™ (glucose oxidase)
7. Gotland	538	24–28	24–28		24–28	≥35	24–28	Yes	Yes	RPG^e^ ≥ 9.0 mmol/L at enrollment week 25, 29, 32/33, 37/38.	FPG < 7.0 and 2-h PG 8.9–11.0	HemoCue AB HemoCue 201 RT (glucose dehydrogenase)
8. Halland	4446	12/ 24–28		24–28	24–28	≥30	24–28	Yes	Yes	RPG^e^ ≥ 8.0 mmol/L at enrollment, week 12, 28/29, 32, 37	FPG < 7.0 and 2-h PG 9.0–11.1	HemoCue AB HemoCue 201 RT (glucose dehydrogenase)
9. Malmö	4944	10–12	10–12			≥35	10–12	Yes	No	Capillary 75 g OGTT week 28 in all women. FPG^e^ ≥ 7 and/or 2-h PG^e^ ≥ 10.0 mmol/L indication for a diagnostic OGTT	FPG ≥7.0 and/or 2-h PG ≥9.0	Roche Cobas (hexokinase)
10. Lund	3703	10–12	10–12			≥35	10–12	Yes	No			
11. Kristianstad	2085	10–12	10–12			≥35	10–12	Yes	No			

Legend: When not otherwise stated, glucose measurement is based on venous plasma

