As the randomisation is on the cluster level and not on the participant level, we will adjust for important prognostic predictors for LGA, such as chronic hypertension, mother’s age, BMI, country of mother’s birth and the mother’s smoking behaviour during pregnancy. Stratification with interaction tests by prognostic factors will be used to further investigate if the associations with LGA between the two diagnostic criteria are heterogeneous and the new diagnostic criteria have an even larger impact in some subgroups according to risk factors.

Because of the stepped wedge study design, some recommended design-specific analyses will be conducted such as stratification by time period to evaluate if the intervention association with outcomes are homogenous during the study time period, or heterogeneity within centres between the two interventions. The secondary adverse neonatal and maternal outcomes will be analysed using the same type of methods and considerations as for the primary outcome. A sub-analysis will be conducted comparing those with fasting glucose 5.1–6.9 mmol/L and/or 2-h glucose 8.5–8.9 mmol/L before and after the switch in criteria.

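### The single glucose band for the sub-analysis does not match the centres' old criteria in Table 1: read literally it admits women diagnosed in both periods, and its 2-h limb fits only four of eleven centres

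*Protocol article*

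**What the plan says.** The last paragraph on analysis methods under Statistics and data analysis defines a sub-analysis "comparing those with fasting glucose 5.1–6.9 mmol/L and/or 2-h glucose 8.5–8.9 mmol/L before and after the switch in criteria". It sets no limits by centre and does not exclude women who already met their centre's old criteria. Under Study design the article announces: "A sub-analysis among those with untreated and treated GDM by the WHO 2013 is also planned". Neither sentence refers to the other, but this band is the only glucose definition given for such a comparison.

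The new criteria are the same everywhere: fasting, "1-h and/or 2-h diagnostic thresholds of ≥5.1, ≥10.0, ≥8.5 mmol/L, respectively". The old criteria differ by centre in Table 1:

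- Stockholm: "FPG < 7.0 and 2-h PG 8.9–11.1". Örebro, Västmanland, Dalarna and Gotland also start their 2-h range at 8.9.
- Halland: "FPG < 7.0 and 2-h PG 9.0–11.1".
- Malmö: "FPG ≥7.0 and/or 2-h PG ≥9.0". The Lund and Kristianstad cells are blank and are read here as covered by the Malmö entry.
- Uppsala and Göteborg: "FPG ≥7.0 and/or 2-h PG ≥10.0". Göteborg also lists a random-glucose route at 12.2 or above.

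The Background gives a different lower end: "The 2 h criteria ranged from 9.0–11.1 mmol/L, using either capillary or venous samples". The section on GDM management guidelines states that treatment and surveillance of diagnosed women were the same before and after the switch.

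**The concern.** Treatment of diagnosed GDM did not change at the switch. A before/after comparison is therefore informative about treatment only in women who are positive by WHO 2013 and negative by their centre's old criteria. A woman positive under both is managed alike in both periods and contributes no treatment contrast. If the band contains many such women, the estimated effect moves towards zero. If the old cut-off differs by centre and the band does not, the group also means something different in each centre. At stake is the interpretation of the sub-analysis aimed at the women whose treatment changes. A null result could be read as no benefit of treating milder hyperglycaemia when part of the group was treated throughout.

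**Working it through.** **Inputs.** The band, the WHO 2013 thresholds, and the old 2-h lower limits and 2017 births from Table 1. The 1-h value is ignored: Study design says it was introduced with the switch, so women positive on it alone cannot be identified before. Their absence from the band is not counted as an error.

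**Rule.** Glucose in steps of 0.1 mmol/L.
- New-positive: fasting ≥5.1 or 2-h ≥8.5.
- Old-positive: fasting ≥7.0 or 2-h ≥ the centre's limit L. Values above the printed upper limits count as already positive.
- Target set: new-positive and not old-positive, that is fasting <7.0, 2-h <L, and either fasting ≥5.1 or 2-h ≥8.5.

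**Where the plan's band is reproduced.** With L = 9.0, the women who change on the 2-h value alone have 2-h 8.5–8.9, which is the stated 2-h limb. The fasting limb 5.1–6.9 matches new-positive and below 7.0. So the 2-h limb is right for the 9.0 centres.

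**Births by old limit (Table 1).**
- 8.9: 28,602 + 3,565 + 3,120 + 3,232 + 538 = 39,057
- 9.0: 4,446 + 4,944 + 3,703 + 2,085 = 15,178
- 10.0: 4,200 + 9,550 = 13,750
- Total 67,985, giving 57.4%, 22.3% and 20.2%.

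**Band against target set, cut-offs as printed.**

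| Old 2-h limit | Centres | In band but old-positive, fasting 5.1–6.9 | In band but old-positive, fasting <5.1 | In target set but outside band |
|---|---|---|---|---|
| 8.9 | 5 | 2-h ≥8.9 | 2-h = 8.9 | none |
| 9.0 | 4 | 2-h ≥9.0 | none | none |
| 10.0 | 2 | 2-h ≥10.0 | none | fasting <5.1, 2-h 9.0–9.9 |

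Example: fasting 5.5 with 2-h 9.5 is in the band, and is old-criteria GDM in nine of the eleven centres.

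**Size.** The documents give no glucose distribution, so this part rests on assumption. Fasting and 2-h values in tested women are taken as bivariate normal: fasting mean 4.6–4.9 and SD 0.40–0.50; 2-h mean 6.4–7.0 and SD 1.4–1.7; correlation 0.2–0.6. All 2⁵ = 32 corners were simulated with one million women each, rounded to 0.1.

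| Quantity | Range over 32 corners |
|---|---|
| Share of band already old-positive, 8.9 centres | 6–37% |
| Share of band already old-positive, 9.0 centres | 5–30% |
| Share of target set missed, 10.0 centres | 1–28% |
| Share missed among those changing on the 2-h value alone, 10.0 centres | 31–54% |

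**Dilution.** If a share s of the band is managed alike in both periods and the rest respond with effect d, the expected contrast is (1 − s)d. For the 8.9 centres this is between (1 − 0.06)d = 0.94d and (1 − 0.37)d = 0.63d. For the 9.0 centres it is between 0.95d and 0.70d.

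**The case against.** The best defence is that the upper limits 6.9 and 8.9 serve little purpose unless they are meant to exclude women already diagnosable under the old criteria. On that reading the fasting limb carries an unstated 2-h ceiling, and the full analysis plan, which is not shown, may say so. This is plausible and may remove the largest inclusion problem. But no text states it, and it does not repair the 2-h limb, which fits only the four 9.0 centres.

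A second defence is that a common band holds the level of glycaemia constant across centres, whereas centre-specific limits make the group differ between them. That is a fair reason to keep the common band as a secondary analysis. It does not make the before-period women untreated.

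Third, the 8.9 overlap is a single 0.1 mmol/L step. It matters much less than the missing 2-h ceiling.

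Some stronger inferences are not supported:

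- A reader might infer that the omission in Uppsala and Göteborg biases the result. It leaves out women on the same glucose rule in both periods, so it narrows the group there.
- A reader might infer that Table 1 contradicts the Background's 9.0 altogether. The Halland and Malmö rows do use 9.0; the conflict is with the five centres at 8.9.
- A reader might take the shares of births as shares of affected women. They describe only the size of the centres concerned.

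**Conclusion.** The point stands as a mismatch between a stated numerical rule and the article's own table. Followed literally, the band admits women already diagnosed under the old criteria in all 11 centres. Its 2-h limb fits centres with 22.3% of births, overlaps the old criterion by one step in centres with 57.4%, and leaves out newly diagnosed women in centres with 20.2%. The direction, dilution towards zero, follows from the criteria and the unchanged management. The size does not: the simulated ranges are wide and rest wholly on the assumed distribution. Two further assumptions are that the band is meant to implement the untreated-versus-treated comparison, and that the Malmö entry covers Lund and Kristianstad.

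A reader might infer that the trial's main result is at risk. It is not: the primary analysis compares LGA in the whole population and does not use this band. The point should be fixed before the sub-analysis is run.

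**What to change.** 1. Reconcile the Background, Table 1 and the sub-analysis sentence: the 8.9 versus 9.0 lower limit, and the Dalarna entry, whose and/or read literally labels every woman with fasting below 7.0. Which clinical cut-off is right is not judged here.
2. Define the group identically in both periods as WHO 2013 positive on the fasting or 2-h value **and** negative by that centre's own documented old criteria, including Göteborg's random-glucose route.
3. State how the region without a fasting sample before the switch is handled. The Background and Study design mention such a region, yet every criterion printed in Table 1 contains a fasting value. One option is to leave it out of the fasting-defined part.
4. Keep the present common band as a sensitivity analysis.

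The cost is a short change of wording, a centre-specific cut-off in the code, and a change in group size. Under the assumptions above, the group shrinks in the nine centres at 8.9 or 9.0, possibly by up to about a third. In the two 10.0 centres it changes by about −4% to +31%, because women with fasting 5.1–6.9 and 2-h ≥10.0 leave while those with 2-h 9.0–9.9 join.

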#### Health economic evaluation

In a first health economic analysis, increased intervention costs for new diagnostic criteria will be set against reduced healthcare costs during pregnancy and in connection with childbirth. This cost analysis consists of 1) estimation of standard cost of treatment of GDM, 2) mother’s healthcare utilization during pregnancy and the month after delivery and, 3) the infant’s health care utilization the month after birth. Data are retrieved from the SPR. Cost of health utilization is estimated based on the Swedish national cost per Patient database.

In a second analysis, the mother’s quality of life during pregnancy and after birth will also be included. It will be expressed in quality adjusted life years (QALY) based on a single item of self-rated health transformed to preference-based values using a Swedish experience based preference valuation [36]. Self-rated health data during pregnancy and after birth is retrieved from the SPR where it is already collected.

In a third analysis, long-term consequences will be modelled. Differences in incidence of LGA will be modelled on future health for the child and cost implications based on best available evidence. In the same way, the mother’s future health impact from intervention can be modelled based on medical risk markers. Cost effectiveness will be expressed in cost per QALY.

## Discussion

To the best of our knowledge, the CDC4G study is the first national SW-CRCT to evaluate the implementation of the 2013 WHO criteria for GDM. There are a number of non-randomised retrospective studies comparing outcomes before and after the change in criteria. Small studies in Spain and Taipei have shown improved pregnancy outcomes switching from the American Diabetes Association (ADA) criteria to the IADPSG criteria on a population basis [37–39]. A non-randomised retrospective study in the USA found no benefit in outcomes [40] but substantial changes in clinical and obstetric care occurred at the same time [41]. The few randomised trials of treating GDM [12–14] have all studied different settings and diagnostic criteria, and a randomised study of the effect on outcomes by treatment on a population level does not exist. Sweden has a public health care system with almost 100% clinical attendance and public health registries with high coverage. With the availability of Swedish registers and possibility to link registers by the personal identification number, this setting provides a unique possibility to evaluate the impacts of the 2013 WHO criteria on pregnancy outcomes and long-term health for both mother and child.

The IADPSG recommend universal screening [18], however, in Sweden there has been a diverse approach to screening as shown in Table 1. Screening criteria at each centre did not change through the trial and should not impact on the validity of the SW-RCT. Since universal screening with both fasting and 2-h values has not been the routine; the existing screening approaches does reduce the number of women who will have received treatment for GDM, in spite of some hyperglycaemia. Furthermore, in practice, many midwives find it difficult to adhere fully to the plethora of screening criteria. Therefore, any benefit (or harms) from GDM treatment will be less than would have occurred with universal screening.

### SW-CRCT: strengths and limitations

The stepped wedge randomised controlled design is particularly beneficial when the intervention is likely to do more good than harm and is mainly used to evaluate routine implementation, as is the case for the CDC4G trial. The design is practical where it is not possible to deliver the intervention to all the participants at the same time for logistical, practical or financial reasons. The stepped wedge design is also appropriate for cost-effectiveness analysis of an intervention on a population basis (i.e. when changes across a whole population/service occur), also making it suitable for the CD4G study.

Disadvantages of the stepped wedge design are difficulties in blinding the participants and those delivering the intervention since the step from control to intervention is evident for both. It is also important to note that the stepped wedge design is likely to lead to a longer trial duration than a traditional parallel design, particularly where effectiveness is measured immediately after implementation. Since the implementation of the new criteria is expected to do more good than harm and is going to continue after the study period there are no real disadvantages from the participant’s point of view. Step-wedge trials can be impacted upon by wider secular trends that can differ between the beginning and end of the study period. In CDC4G, the design has included an alignment, and run in, of all significant clinical policies before the trial commenced, and a clear directive not to introduce any service changes during the study period. A major limitation in cluster randomised trials is the need for larger numbers to overcome the ICC.

### Ethics

Random allocation is performed at the cluster, not the individual level, and prior informed consent to randomisation is not feasible and will not be requested. This is justifiable on the basis that this is a SNBHW policy directive and hence management of GDM is changing as a result of the new national recommendation. It would be unethical not to evaluate the impact of the move, and the best approach for this evaluation is by conducting an RCT. Women always have the right under Swedish Law to change clinic and refuse any aspect of care.

As there is an a priori acceptance that the intervention will do more good than harm [42], rather than belief of equipoise, it may be unethical to withhold the intervention from a proportion of the participants, or to withdraw the intervention as would occur in a cross-over design.

### Trial status

The study preparation period started during 2017 and data collection 1st of January 2018. The first centre was randomised to the 2013 WHO criteria 1st of February 2018 and the last 1st of November 2018. The study is ongoing during 2018 and 2019, with first data collection during 2020.

## Data Availability

Not applicable.

## Abbreviations

ADA: American Diabetes Association
BMI: Body Mass Index
CDC4G: Changing the Diagnostic Criteria for Gestational diabetes
eCRF: electronic case report form
GDM: Gestational diabetes mellitus
HAPO: Hyperglycaemia and Adverse Outcomes
IADPSG: The International Association of the Diabetes and Pregnancy Study Groups
ICC: Inter Cluster Correlation
ISRCTN: International Standard Randomised Controlled Trial Number
LGA: Large for gestational age
NDR: National Diabetes Register
OGTT: Oral glucose tolerance test
QALY: Quality-adjusted life-year
QOL: Quality of life
RCT: Randomised Controlled Trial
SMPGN: Self Measurement of Plasma Glucose
SNBHW: Swedish National Board of Health and Welfares
SNQ: Swedish Neonatal Quality Register
SPR: Swedish Pregnancy Register
SW-CRCT: Stepped wedge cluster randomised controlled trial
T2DM: Type 2 diabetes mellitus
WHO: World Health Organisation
